### Endpoints

The primary endpoint is the CSC at the moment of intraoperative NIR/ICG technology activation after D2 lymphadenectomy performed with the “naked eye.”

The secondary endpoints are the preoperative clinical variables potentially associated with CSC. The other secondary endpoints are as follows: the pattern of abdominal fluorescence distribution according to tumor and patient characteristics, the number of additional lymph nodes retrieved using NIR/ICG technology, the incidence of stage migration due to NIR/ICG application, and the 90-day morbidity and mortality.

### Statistical Analysis

A biostatistician (DG) will perform the statistical analysis. Continuous variables are described as mean (standard deviation) or median (interquartile range) according to distribution; categorical variables are reported as frequency (percentage). Normal distribution of continuous variables is assessed with the Kolmogorov–Smirnov test. Continuous variables are analyzed using Student’s *t*-test or Mann–Whitney test and categorical variables analyzed using Fisher’s exact test or chi-square test as appropriate. All statistical tests are two-sided and a level of <0.05 is used to indicate statistical significance. CSC will be modeled *via* a generalized linear model in the binomial family. The identification of preoperative variables independently associated with CSC will be performed by stepwise selection and using Akaike information criterion (AIC) as benchmark for inclusion. Goodness of fit will be based on the Somers’ Dxy index, adjusted for optimism in accuracy *via* bootstrap resampling (35). A graphic representation of the patterns of fluorescence distribution in the abdominal regions will be represented. Statistical analysis is conducted in R (R Core Team, 2020) (33).

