## Material and Methods

### Objective

The iGreenGO Study aims to investigate whether the intraoperative application of NIR/ICG technology is associated with a change in the surgical conduct (CSC) during curative-intent gastrectomy with D2 lymphadenectomy in a cohort of Western patients affected by AGC.

The preoperative clinical variables potentially associated with CSC will be also investigated.

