### Sample Size Calculation

The sample size is calculated by considering the estimated incidence of intraoperative change in the surgical conduct when using NIR/ICG technology and targeting the precision of the estimates. Data from the literature indirectly suggest an approximate rate of such an event around 17% (27). Perturbing such assumptions (columns) in a sensitivity analysis, the following scenarios are obtained to get an estimated precision of a certain level (rows) with a confidence level of 1 – alpha = 95%, by using the Wilson approach (31, 32). For precisions between 4% and 5%, the expected range of patients will be between 180 and 400, according to adherence to the initial hypothesis made on the incidence of intraoperative change (**Table 1**). This approach in design captures the uncertainty emerging from the literature and the high variability of papers included in the study.

**Table 1 T1:** Sample size calculation.

Incidence of change in surgical conduct							Precision
**20%**	**19%**	**18%**	**17%**	**16%**	**15%**	**14%**	
6,145	5,911	5,668	5,419	5,163	4,896	4,624	**1%**
2,731	2,627	2,518	2,408	2,294	2,176	2,057	**1.50%**
1,535	1,476	1,417	1,354	1,289	1,223	1,157	**2%**
981	944	906	866	826	782	739	**2.50%**
681	655	629	601	574	543	515	**3%**
501	481	462	442	420	400	379	**3.50%**
382	369	352	337	321	307	288	**4%**
302	291	279	266	253	241	229	**4.50%**
245	234	227	217	207	195	186	**5%**

The scenarios are obtained to get an estimated precision (bold values) of a certain level (rows) with a confidence level of 1 – alpha = 95%.

Computations are performed using the R System and the binomSamSize libraries (33, 34).

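### Student's t-test is named with no provision for unequal variances, although a CSC versus no-CSC comparison would split about 1:4 to 1:6; naming Welch's test is a cheap, low-priority improvement

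*Protocol article*

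**What the plan says.** On testing, the Statistical Analysis section says: "Continuous variables are analyzed using Student’s *t*-test or Mann–Whitney test". The check that precedes the choice concerns distribution shape: "Normal distribution of continuous variables is assessed with the Kolmogorov–Smirnov test". The level is common to all tests: "All statistical tests are two-sided and a level of <0.05 is used to indicate statistical significance". The section names neither a variance check nor an unequal-variance form of the t-test, and it does not say which groups the t-test compares.

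The likely grouping comes from the Objective section: "The preoperative clinical variables potentially associated with CSC will be also investigated". The Endpoints section lists those variables as a secondary endpoint. The study has one arm, so any two-group split arises from the data.

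The expected split comes from the Sample Size Calculation section: "Data from the literature indirectly suggest an approximate rate of such an event around 17% (27", with the columns of Table 1 running from 14% to 20%. On size it says: "For precisions between 4% and 5%, the expected range of patients will be between 180 and 400".

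For variables independently associated with CSC, the Statistical Analysis section has a separate method: a binomial generalized linear model with stepwise selection by AIC.

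**The concern.** Student's t-test estimates one common variance, weighted by group size. With roughly five patients without CSC for each patient with CSC, that estimate is mostly the variance of the larger group. The variance of the mean difference, by contrast, depends mostly on the smaller group. If the CSC group is more variable, the standard error is too small and the test of equal means rejects too often. If it is less variable, the standard error is too large and the test rejects too rarely. This happens even with perfectly normal data, so a normality check does not detect it.

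At stake is whether unadjusted p-values for continuous preoperative variables carry the stated two-sided 5% level.

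**Working it through.** **Inputs.** CSC rate 17%, range 14% to 20% (Sample Size Calculation, Table 1). N = 217 for 5% precision and N = 337 for 4% precision at 17% (Table 1). Two-sided level 0.05 (Statistical Analysis). The SD ratio r = SD in CSC / SD in no CSC is not in the article, so it is assumed and shown as a range. Data are taken as normal with equal means.

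**Step 1: the plan's own figure.** The Wilson half-width is z·√n/(n + z²) · √(p(1 − p) + z²/(4n)), with z = 1.96. At p = 0.17 and n = 217:

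1.96 × 14.731/220.84 × √(0.1411 + 0.0044) = 0.1307 × 0.3815 = 0.0499.

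This agrees with the 5% row. The smallest n is 216 for 5% and 338 for 4%, against 217 and 337 in the table. All 63 cells of Table 1 reproduce within a small tolerance, so the sample sizes are not in question.

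**Step 2: group sizes.** The ratio of no CSC to CSC is (1 − p)/p:
- 14%: 0.86/0.14 = 6.1
- 17%: 0.83/0.17 = 4.9
- 20%: 0.80/0.20 = 4.0

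At N = 217 and 17%, the groups are 37 and 180.

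**Step 3: true level of the pooled test.** Set the SD without CSC to 1, with n₁ = 37 and n₂ = 180.
- Variance the test uses: A = [(36r² + 179)/215] × (1/37 + 1/180)
- True variance of the mean difference: B = r²/37 + 1/180
- Large-sample true level: 2·[1 − Φ(1.96·√(A/B))]

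For r = 1.5:
- pooled variance = (36 × 2.25 + 179)/215 = 1.2093
- A = 1.2093 × 0.03258 = 0.0394
- B = 2.25/37 + 1/180 = 0.0664
- √(A/B) = √0.594 = 0.7705
- 1.96 × 0.7705 = 1.510, so the level is 13.1%

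The other ratios, beside simulation with 200,000 datasets each:

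| SD ratio (CSC / no CSC) | Formula | Student, simulated |
|---|---|---|
| 0.67 | 1.1% | 1.2% |
| 0.8 | 2.3% | 2.3% |
| 0.9 | 3.6% | 3.5% |
| 1.0 | 5.0% | 5.0% |
| 1.1 | 6.6% | 6.6% |
| 1.25 | 9.0% | 9.1% |
| 1.5 | 13.1% | 13.1% |
| 2.0 | 19.8% | 19.8% |

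Welch's test holds 4.9% to 5.2% in every scenario.

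**Step 4: sensitivity.** Over N = 186 to 382 and CSC rates of 14% to 20%, Student's test gives 0.9% to 1.4% at r = 0.67 and 12% to 14% at r = 1.5. Total N hardly matters: 57 versus 280 (N = 337) also gives 13.1% at r = 1.5.

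**Step 5: the other named test.** Mann–Whitney at 37 versus 180 rejects in about 9.3% of datasets at r = 1.5 and 11.4% at r = 2.0 (6,000 simulations each). It is chosen on normality, so unequal variance in normal data would not trigger it, and it would not restore the level if it did.

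**Step 6: price of Welch.** With equal variances and a true difference of 0.5 SD, power at 37 versus 180 is 78.8% for Student and 77.4% for Welch.

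**The case against.** The strongest objection is that an article condenses its analysis section, and the form of the t-test is a detail often left to the analysis plan. That lowers the weight of the point but does not remove it. The article does not leave the test open: it names Student's, and ties the choice against Mann–Whitney to normality only.

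Further objections stand and limit the point:
- The pooled form is inferred from the test's name, and the CSC grouping is inferred from the objective. Other comparisons, such as fluorescence pattern by patient characteristics, could split quite differently.
- No SDs are given, and nothing in the article suggests an SD ratio as large as 1.5 for any preoperative variable.
- The article does not make a t-test p-value a condition for entry to the binomial model.
- The change leaves the Mann–Whitney branch as it is.

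Three stronger readings are tempting, and the document supports none of them. A reader might infer that any variance difference takes the level far from 5%; a 10% difference in SD takes it only to about 3.5% or 6.6%. A reader might infer that the plan will declare associations where none exist; a variable fully independent of CSC has the same distribution, and so the same variance, in both groups, and Student's test then holds its level. The distortion concerns the test of equal means when the spread differs by CSC status. A reader might also infer that the identification of predictors is undermined; that rests on the binomial model with AIC. Nor is tumour size a good example, because the Pathology section lists it among the specimen variables. Age is a better one.

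**Conclusion.** The point holds in a limited form and with low priority. Student's t-test is named without any provision for unequal variances, in a study whose own CSC rates would make CSC versus no-CSC groups about 1:4 to 1:6. At 37 versus 180, a moderate SD difference moves the true level of the test of equal means to about 2.3% (ratio 0.8) or 9% (ratio 1.25), and a larger one to about 1.2% (0.67) or 13% (1.5).

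This rests on three assumptions: that Student's means the pooled form, that the groups are CSC yes and no, and that the SDs differ at least moderately. Only the supportive univariable comparisons of preoperative continuous variables are exposed. The primary CSC proportion, its Wilson-based sample size and the binomial model are untouched.

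**What to change.** In the Statistical Analysis section, name Welch's unequal-variance t-test in place of Student's for comparisons of continuous variables between CSC and no-CSC patients, and say that these are the groups compared. Report the mean difference with its Welch 95% CI beside the p-value.

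The cost is a change of wording and, if the variances are in fact equal, about 1 percentage point of power (78.8% against 77.4% in the example above). No extra patients, data or design changes are needed.

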### Study Design and Setting

The iGreenGO Study is a single-arm prospective observational multicentric study. National and international academic and non-academic hospitals are invited to participate in the study. The duration of the study will be approximately 4 years (3 years for inclusion, 1 year for data analysis and results publication). The enrolment of patients has started since September 2021.

All procedures will be in accordance with the ethical standards of the responsible committee on human experimentation (institutional and regional) and with the Helsinki Declaration of 1975, as revised in Brazil 2013 (28). The Local Ethical Committee reviewed and approved the protocol (380-09062021). The protocol is registered at *clinicaltrial.gov* (NCT04943484). Study results will be reported according to Strengthening the Reporting of Observational Studies in Epidemiology (STROBE) statements (29).

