## Study Limitations

The iGreenGO Study presents several potential limitations: first of all, the time interval for ICG injection is wide, potentially generating heterogeneity in the methods between participating centers. However, the ideal time for ICG injection is not universally established and a wide time interval is necessary in order to encounter clinical practice and organizational aspects of all participating centers. In addition, in the case of stenotic cancers, ICG injection can be performed at four proximal tumor points. In this case, the injections and the lymph nodes seen may not be representative of all the lymphatic drainage pathways. However, specific subgroup analyses were performed in order to mitigate this possible bias.

Lastly, the sequence for D2 nodal station dissection is not standardized and it is left to the preference of each participating center. However, the pictures taken after lymphadenectomy and the sole inclusion of centers that have performed at least 20 gastrectomies *via* a minimally invasive approach before participating in the study aim to offset these differences. Furthermore, the inclusion of different surgical approaches (laparoscopic and robotic) should increase the reproducibility of the results.

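### The 4–5% precision for the CSC rate assumes independent patients, and clustering by centre would widen it by an amount that depends on an unstated ICC and centre count

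*Protocol article*

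**What the plan says.** **Sample size.** Under Sample Size Calculation, the protocol article starts from the literature: "Data from the literature indirectly suggest an approximate rate of such an event around 17" percent. Table 1 then gives patient numbers "with a confidence level of 1 – alpha = 95%, by using the Wilson approach". The resulting plan reads: "For precisions between 4% and 5%, the expected range of patients will be between 180 and 400". The software is a single-proportion sample-size package: "Computations are performed using the R System and the binomSamSize libraries". The sensitivity analysis varies the CSC rate and the precision and nothing else. No number of centres, ICC or design effect appears.

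**Analysis.** Statistical Analysis models CSC by "a generalized linear model in the binomial family", with AIC-based stepwise selection of preoperative variables and a bootstrap correction of Somers' Dxy. It names no centre or surgeon effect and no robust variance.

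**Setting.** Under Study Design and Setting: "National and international academic and non-academic hospitals are invited to participate in the study". Step 4 defines CSC by fluorescence that persists after the team's own white-light D2 dissection and calls for more dissection. Study Limitations accepts that the wide injection window may make methods differ between centres, and that "the sequence for D2 nodal station dissection is not standardized and it is left to the preference of each participating center".

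**The concern.** CSC is partly a measure of the operating team. It depends on how complete that team's dissection was before the camera was switched to fluorescence, and on its judgement that what still glows needs removing. The protocol names two further sources of between-centre difference, injection timing and dissection sequence. Patients treated in one centre may therefore resemble each other in CSC more than patients from different centres do.

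The Wilson calculation gives every patient full weight as independent information. With positive intra-centre correlation the effective sample size is smaller than N. The interval for the primary rate would then be narrower than its true uncertainty and would cover less often than 95%. This matters because precision of the CSC rate is the only criterion on which the study is sized.

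In the secondary model, ignoring clustering mainly understates standard errors for covariates that vary between centres. Robotic versus laparoscopic approach is an example, so far as it follows the centre's practice. A centre difference could then pass as an association with such a covariate.

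**Working it through.** **Inputs from the protocol article:** CSC rate p = 0.17; 95% confidence, z = 1.96; Wilson interval; N = 217 (5%) and 337 (4%) from Table 1; upper end of the stated range, N = 400.

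**Assumed, because not stated:** equal centres of m = 10 or 20 patients; ICC 0.02, 0.05 or 0.10.

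**Step 1: reproduce Table 1.** Wilson half-width = z√n/(n+z²) × √(p(1−p) + z²/(4n)).
- n = 217: 28.87/220.84 × √(0.1411 + 0.0044) = 0.1307 × 0.3815 = 4.99%.
- n = 337: 35.98/340.84 × √(0.1411 + 0.0028) = 0.1056 × 0.3794 = 4.01%.

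The smallest n meeting each target is 216 for 5% and 338 for 4%, against 217 and 337 printed. All 63 cells agree within 0.85%. Table 1 is arithmetically sound, and it is reproduced with no allowance for clustering.

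**Step 2: add clustering.** Design effect DE = 1 + (m−1) × ICC; effective n = N/DE; half-width from the Step 1 formula at effective n; approximate coverage of the unadjusted interval = 2Φ(1.96/√DE) − 1.

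| m | ICC | DE | Half-width, N=217 | Half-width, N=337 | Coverage |
|---|---|---|---|---|---|
| – | 0 | 1.00 | 4.99% | 4.01% | 95% |
| 10 | 0.02 | 1.18 | 5.42% | 4.35% | 92.9% |
| 10 | 0.05 | 1.45 | 6.00% | 4.82% | 89.6% |
| 10 | 0.10 | 1.90 | 6.86% | 5.51% | 84.5% |
| 20 | 0.02 | 1.38 | 5.85% | 4.70% | 90.5% |
| 20 | 0.05 | 1.95 | 6.95% | 5.59% | 84.0% |
| 20 | 0.10 | 2.90 | 8.46% | 6.80% | 75.0% |

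A beta-binomial simulation of the unadjusted Wilson interval with 20 equal centres points the same way. At ICC 0.02, 0.05 and 0.10, coverage was about 92%, 88% and 82% at N=217, and 91%, 86% and 78% at N=337.

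**Step 3: where is 5% lost?** A 5% half-width needs an effective n of about 216.
- N = 217: there is no slack, so in effect any positive ICC exceeds 5%.
- N = 337: DE may reach 337/216 = 1.56, that is, ICC 0.56/9 = 0.06 at m = 10, or 0.56/19 = 0.03 at m = 20.
- N = 400: DE may reach 400/216 = 1.85, that is, ICC 0.85/9 = 0.09 at m = 10, or 0.85/19 = 0.045 at m = 20.

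**Step 4: would more patients help?** With K centres fixed, effective n cannot exceed K/ICC. For 10 centres and ICC 0.05 that is 10/0.05 = 200, below 216, so no enrolment in those centres reaches 5%. With 20 centres and ICC 0.05, about 451 patients would be needed for 5%.

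**The case against.** Several points can be made for the plan.

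- **Size.** A reader might infer that the intervals are bound to be too narrow and that the 4–5% precision will not be achieved. The documents do not support that. They give neither ICC nor number of centres, and at ICC 0.02 the half-width at N=337 stays inside the band for both centre sizes shown. This stands.
- **Role of the model.** A reader might take the binomial model to supply the interval for the primary rate. It is described in connection with finding preoperative variables associated with CSC, which is a secondary endpoint. The section does not specify the primary interval. This stands, and the firm anchor is therefore the sample size section.
- **Silence on centre.** A binomial model does not rule out a centre term or robust variance, and a condensed article may leave these to an analysis plan that is not shown. This stands for the model. It does not answer the precision statement, which the article itself fixes and which is reproduced under independence.
- **Covariates.** Neoadjuvant treatment is decided patient by patient, and injection time can vary within a centre. For covariates that vary within centres, standard errors need not be too small. This stands.
- **Target of inference.** For the rate in the participating centres alone, taken as fixed, the binomial interval is not anti-conservative. This stands as a condition. The stated aim, however, is to clarify the role of the technology in Western surgery, which reaches further.
- **Mitigation.** Centres need at least 20 minimally invasive gastrectomies, send photographs taken before fluorescence is activated, and are assessed against published completeness criteria; most use one described technique. This makes a high ICC less likely, but it is not an analysis method and does not make the ICC zero.

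**Conclusion.** The concern holds in a conditional form. The precision in Table 1 is correct for independent patients only, while the protocol describes an outcome that depends on the operating team and concedes differences between centres. If CSC varies between centres and the result is to apply beyond those taking part, a simple Wilson interval understates the uncertainty. The direction is firm for any positive ICC; the size rests on assumed ICC and centre size. At N=217 the 5% target is lost, moderately at ICC 0.02 and clearly at 0.10. At N=337 to 400 it survives small ICC and fails only with larger ICC or larger centres. It would go too far to say that the study misses its precision, or that its analysts will ignore centre. The point on the model is secondary and mainly concerns covariates that vary between centres.

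**What to change.** 1. **Sample Size Calculation:** state that Table 1 assumes independent patients. Add the expected number of centres and a small table of half-widths over a range of ICC, for example 0.02 to 0.10. Restate the precision; do not enrol more for this reason.
2. **Primary endpoint:** report the CSC rate with a cluster-adjusted 95% interval, for example Wilson at n divided by the estimated design effect.
3. **Secondary model:** fit CSC with a centre random intercept, or by GEE with small-sample robust errors, and resample centres rather than patients in the bootstrap. If an existing analysis plan already does this, a cross-reference is enough.

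**Cost:** some wording, one table and a little more analysis work. Centre is already known, so no new data are needed. The downside is wider intervals.

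### Somers' Dxy measures discrimination, not goodness of fit, and stepwise AIC selection does not support calling the retained variables independently associated with change in surgical conduct (CSC)

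*Protocol article*

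**What the plan says.** The Statistical Analysis section of the protocol article models CSC with a generalized linear model in the binomial family and fixes two things about it.

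- **Selection.** Preoperative variables independently associated with CSC are to be found by "stepwise selection and using Akaike information criterion (AIC) as benchmark for inclusion".
- **Fit.** "Goodness of fit will be based on the Somers’ Dxy index", with a bootstrap adjustment for optimism. The section names no other measure of fit.

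The same section says "All statistical tests are two-sided and a level of <0.05 is used to indicate statistical significance".

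The preoperative variables linked to CSC are part of the Objective, the first-listed secondary endpoint under Endpoints, and part of the Conclusion. Those sections speak only of potential association; the claim of independent association appears in Statistical Analysis. The sample size was set only by the precision of the CSC incidence: "For precisions between 4% and 5%, the expected range of patients will be between 180 and 400". The article gives neither the number nor the list of candidate variables.

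**The concern.** A goodness-of-fit measure should show whether predicted probabilities agree with observed frequencies. Dxy cannot, because any monotone distortion of the predictions leaves it unchanged. It is uninformative in the other direction too: a correctly specified model with weak predictors has a low Dxy without any lack of fit.

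Stepwise AIC is a rule for choosing a model by estimated predictive loss. It admits weak terms by design, and the final model is then reported as if its terms had been chosen in advance. A reader told that a variable is independently associated with CSC will take it as an established finding, which this procedure does not provide. At stake is the list of predictors that the study intends to publish as its leading secondary result.

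**Working it through.** **1. The plan's own sample sizes.** Sample Size Calculation uses the Wilson interval at 95%, with precision read as the half-width:

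h = z/(1 + z²/n) × √[p(1 − p)/n + z²/(4n²)], z = 1.96.

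At p = 0.17 and n = 217, h = 0.0499, as Table 1 states for 5%. Solving for the smallest n gives 216 at 5% (table: 217) and 338 at 4% (table: 337). All 63 cells of Table 1 reproduce to within 0.9%.

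**2. Expected events.** The 4% row reads "382 369 352 337 321 307 288" and the 5% row "245 234 227 217 207 195 186", for incidences of 20% down to 14%.

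- At 17%: 217 × 0.17 = 36.9 and 337 × 0.17 = 57.3, so about 37 to 57 events.
- Across the table: 186 × 0.14 = 26.0 and 382 × 0.20 = 76.4, so about 26 to 76 events.

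**3. What Dxy can see.** Dxy = 2(C − 0.5), where C is the probability that a patient with CSC is ranked above one without. A simulated data set of 400 patients with 17.0% observed events illustrates this:

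| Predictions | Dxy | Mean predicted risk |
|---|---|---|
| True model | 0.520 | 0.168 |
| Slope tripled | 0.520 | 0.285 |
| Intercept shifted by +2 | 0.520 | 0.518 |

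The index is identical in all three. Bootstrap correction subtracts optimism from this same rank statistic, so the corrected value is equally blind.

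**4. The level implied by AIC.** AIC = −2 log L + 2k, so a one-degree-of-freedom term is kept when its likelihood-ratio chi-square exceeds 2: P(χ²₁ > 2) = 0.157.

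**5. Chance of keeping noise.** The candidate count is not in the article. I assume 5 to 20 independent one-degree-of-freedom candidates, all unrelated to CSC. P(at least one kept) = 1 − (1 − 0.157)^k, and the expected number kept is 0.157k:

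| k | At least one kept | Expected number kept |
|---|---|---|
| 5 | 58% | 0.8 |
| 10 | 82% | 1.6 |
| 15 | 92% | 2.4 |
| 20 | 97% | 3.1 |

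A simulation of two-way stepwise AIC logistic regression at 17% incidence (300 runs per setting) agrees:

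| k | N | At least one kept | Mean kept | Mean kept with p < 0.05 |
|---|---|---|---|---|
| 10 | 180 | 82% | 1.72 | 0.52 |
| 10 | 400 | 85% | 1.71 | 0.52 |
| 15 | 180 | 95% | 2.64 | 0.79 |
| 15 | 400 | 93% | 2.52 | 0.81 |

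The rate hardly changes with N.

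**6. P-values after selection.** Among retained noise terms, the share with p < 0.05 is 0.52/1.72 = 30%, 0.52/1.71 = 30%, 0.79/2.64 = 30% and 0.81/2.52 = 32%. This is close to 0.05/0.157 = 32%, and far from the nominal 5%. A p-value from the final model therefore does not have its usual meaning for a variable that is in the model because it was selected.

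**7. What few events do.** Mean apparent Dxy on pure noise was 0.23 (k = 10) and 0.31 (k = 15) at N = 180, against 0.16 and 0.21 at N = 400. Fewer events raise optimism, not the number of false inclusions.

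**The case against.** Much of the case on the other side stands, and it limits the point. Five stronger readings are tempting.

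- **The small number of events causes the false inclusions.** It does not: the rate is the same at 180 and 400 patients. Multiplying the 17% rate by 180 and 400 to get 31 to 68 events also mixes scenarios, because those limits span other incidences.
- **AIC manufactures significant predictors.** In the simulation at least one retained term had p < 0.05 in 39–41% of runs (10 candidates) and 53–55% (15). Testing the same candidates without selection gives 1 − 0.95^10 = 40% and 1 − 0.95^15 = 54%. That is ordinary multiplicity.
- **The reported Dxy will look good on noise.** The apparent values above are not what the plan reports. With 12 noise candidates and selection repeated inside the bootstrap (40 data sets, 30 resamples each), Dxy fell from 0.24 to 0.04 at N = 217 and from 0.18 to 0.03 at N = 400. The article does not say whether selection is repeated, a detail that a full plan may settle.
- **The 0.05 level contradicts the AIC rule.** It does not. One governs tests, the other model inclusion.
- **The missing candidate list is a fault.** A condensed article may leave it to the full plan, and the list may be short.

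It is also fair that a maximum-likelihood logistic model with an intercept matches mean predicted to observed risk in its own data. The distorted predictions above illustrate a property of Dxy; they do not forecast this model's behaviour. Nor does the article propose a risk score. But the plan itself promises an assessment of fit, and the named index does not deliver one. The label of independent association likewise goes beyond what the stated selection rule supports.

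**Conclusion.** The point holds in limited form. Dxy is misnamed as goodness of fit whatever the candidate list turns out to be. The label of independent association is not supported by stepwise AIC, which works at p < 0.157 for a one-degree-of-freedom term and leaves p-values and intervals that ignore the selection.

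The 58% to 97% range is conditional. It assumes 5 to 20 candidates that are independent, one-degree-of-freedom and all noise. The last is a worst case, and the count is not stated, so a false inclusion is likely rather than certain. Few events, about 37 to 57 at 17% incidence, add instability and optimism.

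The consequence is confined to the secondary analysis of predictors. The primary estimate of CSC incidence and its sample size are unaffected.

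**What to change.** 1. Describe Dxy as the discrimination measure. Assess fit by calibration intercept and slope, optimism-corrected in the bootstrap already planned. The correction is needed because, in the data used to fit an unpenalised model, intercept and slope are 0 and 1 by construction.
2. Choose one of two routes for the predictors:
   - report a pre-specified full model, all terms shown, without selection; or
   - keep AIC, repeat the whole selection in every bootstrap sample, and report how often each variable is included.
3. If AIC is kept, describe retained variables as exploratory candidates. This also brings Statistical Analysis into line with the more cautious wording of the Objective and Endpoints sections.

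The length of the candidate list and any penalised estimation are for the study team to decide. For orientation, 10 candidates against 37 to 57 events is 3.7 to 5.7 events per candidate.

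The cost is a change of wording, some extra code and a more cautious secondary conclusion. No new data and no change to the sample size are needed.
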